## **5 PURPOSE**

This project seeks to address the above gaps by conducting outcomes evaluation research regarding the routine use of electronically administered QOL assessment instruments as practice support tools in the

home care of patients who have chronic life-limiting illnesses. Specifically, our proposed study is guided by four overarching aims and related research questions:

**AIM 1:** To examine the efficacy of the QPSS in home care for older adults who have advancing life-limiting illnesses.

- Does the routine use of the QPSS in home care improve quality of care, as indicated by patients' and family caregivers' reports of enhanced QOL and experiences with the care provided?

**AIM 2:** To evaluate the cost consequences of implementing the QPSS in home care.

**AIM 3:** To understand the process of implementing the QPSS in home care.

- How can we best facilitate the integration and routine use of the QPSS in the home care for older adults who have advancing life-limiting illnesses and their family caregivers?

**AIM 4:** To examine how integration of the QPSS with health information systems will meet the needs of administrators for quality improvement and accreditation.

**For the first aim,** we will conduct a randomised controlled trial (RCT) to evaluate the impact of using the QPSS on QOL and health care experiences of patients and their family caregivers by testing the following **hypotheses:** Use of the QPSS in routine home care clinical practice will result in improved QOL [primary outcome] for older adults who have life-limiting illnesses [Hypothesis 1] and for their family caregivers [Hypothesis 2], as well as increased patient [Hypothesis 3] and family caregiver [Hypothesis 4] satisfaction with care [secondary outcome] compared with these measures in patients and caregivers who receive usual home care.

**For the second aim,** we will evaluate the impact of implementing the QPSS on resource use and costs (health care *and* non-health care costs) from a cost-consequences to society perspective (consequence analysis framework), which will be complemented by a cost-utility analysis.

**For the third aim,** we will examine how the QPSS is being used in practice. Specifically, we will use mixed methods to (a) understand clinicians', patients', and family caregivers' points of view about how to adapt and integrate the QPSS intervention into clinical practice at each home care office; (b) examine how the QPSS is used to support care planning locally by linking assessment data to procedures adopted at each home care office and tracking interventions and practices of the interdisciplinary team to address patient and caregiver QOL concerns, and (c) evaluate the process of using the QPSS in home health care.

**For the fourth aim,** we will examine how the QPSS can be integrated broadly with other health information systems to meet the needs of administrators at various levels (home care office; health authority; Ministry of Health) and enable patient- and family-centered analytics for continuous quality improvement and accreditation. Actual integration will not occur during the project.

## 6 METHODS

### 6.1 Overview of Research Design

The original REB application involved only the focus groups. This amendment pertains to the randomized control trial (RCT) and process evaluation in Stage 2 of the project. The research design for all three stages is briefly described so that it is clear how each stage relates to the overall project. The economic evaluation component of Stage 2 and the sustainability study in Stage 3 will be detailed in a future amendment for research ethics approval.

This project is for the evaluation of both the process of implementing the QPSS into home care practice and the outcomes resulting from it. The use of the QPSS is a complex intervention because it has several interrelated components, presents several challenges for evaluators, and has methodological and practical complications that must be addressed. Adaptation of the intervention to local context and engagement of local health care teams is critical for successful implementation. We will take an action-oriented approach by applying the CIHR Knowledge to Action (KTA) Framework in three stages (see [Appendix 3](#)), and involve clinicians, administrators, patients, and family caregivers in the adaptation and integration of the QPSS into routine practice. We will assess facilitators and barriers to the use of the QPSS find ways of overcoming barriers, implement the QPSS in routine care, evaluate outcomes, and sustain knowledge use.

#### 6.1.1 Stages of the research project

**Stage 1: Local adaptation** (one year at each home care office).

- Pre-intervention measurement of QOL and health care experience outcomes (prior to use of the QPSS).
- Iterative qualitative data collection and analysis to guide adaptation and integration of the QPSS intervention in local settings (home care offices), which will also inform **Aim 3**.
- Development of site-specific protocols for QPSS integration into routine daily practice. These protocols will be iteratively adapted to changing healthcare delivery systems over the duration of Stage 1.
- Once the QPSS is adapted for local use and a protocol for integration into practice elaborated, clinicians will receive education about the QPSS and how to integrate it into their practice, and then integrate it into practice in the last 6 months of Year 1 at their site as a period of transition. Data of the patients and family caregiver who participate in the transition phase will not be collected as part of outcome evaluation.

**Stage 2: Evaluation** (one year at each home care office). Focusing on the KTA phases of monitoring knowledge use and evaluating outcomes, this stage will involve:

- Conducting a RCT to evaluate the impact using the QPSS on the QOL and health care experiences of patients and family caregivers (**Aim 1**).
- Conducting an economic evaluation to estimate the cost consequences (and cost-utility) of implementing the QPSS in home care (**Aim 2**).
- Applying qualitative and quantitative methods to examine the process of QPSS use in home care (**Aim 3**).

**Stage 3: Sustainability** (from the end of Stage 2, which depends on the timing of enrollment of each home care office to six months prior to the end of the grant). This stage will be guided by the last part of the KTA framework aimed at local sustainability and dissemination of lessons learned. Specifically, Stage 3 will include:

- Examining the integration of the QPSS with other health information systems and use of QPSS data by health care administrators (**Aim 4**).
- Discussion of results of all parts of the evaluation among the team members regarding whether sustained and more widespread integration into practice is warranted.
- If the results warrant, discussion among team members as to how to scale up the intervention.
- Broad dissemination of the results and lessons learned.

### 6.1.2 Experimental design

To test the hypotheses for Aim 1, we will conduct a two-arm parallel RCT with treatment and control groups (Stage 2). Patients and their family caregivers recruited in Stage 2 will be randomly assigned to a treatment group (clinicians use the QPSS and have access to QPSS data) or control group (clinicians do not use the QPSS and will not have access to the QPSS data), stratified by site. Stratification is necessary because the intervention protocol may not be identical for the different home care offices. To explore the possibility of contamination (since clinicians will be caring for patients and caregivers in both arms) and the potential impact of changes in the health care system between Stages 1 and 2, we will also collect outcomes data collection from a pre-intervention group consisting of QPSS-naïve patients and family caregivers enrolled during the 12 months of Stage 1 at each site, before the QPSS is used in practice.

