STAGE 1: The **local adaptation stage** will use qualitative methods (user-centered design focus groups and interviews with clinicians, managers, patients, and family caregivers) to adapt the QPSS to the unique context of each site and develop protocols for its routine integration in daily practice. To test the recruitment and data collection procedures and explore the possibility of contamination and the potential impact of changes in the health care system between Stages 1 and 2, this will also include (a) measurement of patient and family caregiver QOL and health care experiences prior to routine use of the QPSS in home care to serve as a pre-intervention comparator group (Aim 1) and (b) data collection regarding the cost of local adaptation and training (Aim 2).

TRANSITION PHASE: In the last 6 months of Stage 1, a few clinicians from each site will explore the use of the QPSS with 1 to 2 of the clients in their respective caseload. The clinicians trying out the QPSS will provide feedback on their experience using the system via focus group (in Stage 1) and through one-time individual interview. Clients and family caregivers who tried out the QPSS will also be interviewed. The feedback from clinicians, clients and family caregivers will inform the development of the site protocol, as well as the preparation for QPSS implementation in Stage 2.

STAGE 2: During the **evaluation stage**, we will (a) conduct a randomized controlled trial (RCT) to evaluate the impact of using the QPSS on the QOL and care experiences of patients and their family caregivers (Aim 1); (b) conduct an economic evaluation to estimate the cost consequences of the QPSS in home care (Aim 2) in the last six months of Stage 2; and (c) apply qualitative and quantitative methods to examine the use of the QPSS in home health care (Aim 3).

STAGE 3: The **sustainability stage** will focus on (a) whether the results warrant sustained and widespread integration of the QPSS into practice, and if so, (b) how to scale this up, (c) how to further integrate the QPSS with other health information systems to facilitate use by health care administrators for continuous quality improvement and accreditation (Aim 4) and (d) dissemination of results.

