## 6.2 **Methods for Stage 1: Local integration and exploratory use of the QPSS intervention**

Qualitative methods, including focus groups with clinicians and managers, as well as interviews with patients and family caregivers at each site, will be used with the goals of tailoring the QPSS intervention to each local practice setting and developing site-specific implementation protocols. In Stage 1, at each home care office we will: (a) determine the selection of appropriate QOL assessment instruments to be implemented in clinical practice using the QPSS; (b) address barriers and identify facilitators for workflow integration; (c) work with the health care teams to identify site-specific practices and interventions to address concerns that may be identified by the patients and family caregivers in Stage 2 (the range of concerns that may be identified will be determined by the locally selected QOL assessment instruments); and (d) finalize an implementation protocol for integration of the QPSS into routine practice. During the last six months of Stage 1, we will have the clinicians at each home care office explore the use of the QPSS intervention in practice (transition period) (see [Appendix 4](#)).

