### 6.3.6 Contamination

Clinicians who perceive a positive impact on their practice through awareness of the QOL scores of their patients and family caregivers in the intervention group may change their practice to more comprehensively assess QOL for their other patients, some of which may be in the control group. Patients and family caregivers in the control group may choose to discuss their QOL more with their health care providers, or even print and share their completed QOL questionnaires. These are desirable outcomes, but in an RCT, it is considered contamination. Therefore, no effort will be made to either encourage or prevent this, but we will assess such contamination in two ways. First, as stated above, the QOL and experience

with health care scores of patients and family caregivers from the pre-intervention group (collected in Stage 1) will be compared to the scores of the control group (Stage 2). Second, clinicians participating in focus groups and individual interviews will be asked to describe any change they've noticed in their general practice related to their experience with the intervention group (see revised clinicians focus group guide in [Appendix 16](#) and interview guide in [Appendix 29](#)).

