#### **6.4.1.4 *Transition phase***

For the transition phase during Stage 1, 2 to 4 clinicians participating in the focus groups at each home health offices will explore use of the QPSS with 1 to 2 of their patient(s) and family caregiver(s) of their choice who are not providing pre-intervention outcomes evaluation data. Clinicians who have used the QPSS in the transition phase of Stage 1 will be interviewed about their experience in using the QPSS, in addition to providing feedback at the focus groups. All home care offices are currently enrolled in Stage 1 of the project.

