#### 6.4.2.5 *Stage 2*

For the RCT, we will recruit a total of 360 patients and 360 family caregivers across all sites (see [Appendix 4](#)). The number of participants at each site will vary depending on the size of the site. The RCT participants may include Stage 1 participants, but will not include individuals who have used the QPSS in the transition phase; they may choose to continue using the QPSS if they wish but any data they provide will not be used in the study. Eighteen to twenty-four of the RCT participants will be interviewed about their experiences using the QPSS during this stage. The interviewees will be purposively sampled from the intervention arm, to achieve diversity in gender, age, health condition, and family caregivers' relationship (e.g., spouse, child, or friend).

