“Hello Mr/Mrs/Ms, it’s (caller name) calling from Trinity Western University/University of Alberta. I’m following up with the information you’ve received regarding the study on integrating a quality of life assessment and practice support system in homecare services for older adults with chronic illness and their families. It’s (date and time). I will call you again tomorrow morning. You can also call me anytime tomorrow at the call-back number ([name] for TWU). Thank you very much and I look forward to speaking with you.”

*6.5.2.2 Transition phase*

The initial contact with potential participants will be made by a clinician who is: 1) responsible for providing care in the home, and 2) participating in exploring use of the QPSS. Patients and family

caregivers who are eligible (see inclusion criteria above on page 21) will be invited to use the QPSS. The clinician responsible for patient care will confirm eligibility of the patients and family caregivers. Eligible patients and family caregivers include those who meet the inclusion criteria and are not part of pre-intervention comparator group or who are part of the pre-intervention group but have already completed responding to the four administrations of the pre-intervention questionnaire (i.e., after recruitment for the pre-intervention group has been completed). The clinician will explain the study using the following script:

“In Fraser Health homecare/Alberta Health Services, we are currently conducting a research project to understand if and how we can improve our care to you by using an electronic system called the QPSS. We would like to invite people to try using the system. If you are interested and permit the research team to contact you for this project, I will give the research team your phone number.”

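### The pre-intervention versus control comparison cannot reliably isolate or rule out contamination: its window overlaps QPSS use, people may be in both groups, and its schedule is stated inconsistently

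*Protocol*

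**What the plan says.** **Purpose.** Clinicians look after patients in both arms (Protocol 6.1.2), and 6.3.6 makes no attempt to prevent contamination. It will be assessed in two ways: by comparing pre-intervention scores with control scores, and by asking clinicians in focus groups and interviews about changes in their general practice. Sections 2, 6.1.2 and 6.2.2 use the same pre-intervention group to explore health-system change between the stages.

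**Window.** Section 6.1.2 has the comparator "enrolled during the 12 months of Stage 1 at each site, before the QPSS is used in practice", and 6.2.2 likewise places its data collection before use. Yet section 2 states: "In the last 6 months of Stage 1, a few clinicians from each site will explore the use of the QPSS". Section 6.2 agrees: "During the last six months of Stage 1, we will have the clinicians at each home care office explore the use of the QPSS". Section 6.1.1 says that clinicians, once trained, will "integrate it into practice in the last 6 months of Year 1 at their site as a period of transition". Section 6.6.2.1 collects comparator data every two months in the 12 months of Stage 1.

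**Scale of early use.** Section 6.4.1.4: "2 to 4 clinicians participating in the focus groups at each home health offices will explore use of the QPSS with 1 to 2" (the last figure counts patients, with their caregivers, per clinician). Section 6.1.1 keeps these users' data out of the outcome evaluation.

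**Membership.** Section 6.4.2.5: "The RCT participants may include Stage 1 participants". Section 6.5.2.3 actively invites them, except transition-phase users.

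**Schedule.** Section 6.5.2.2 refers to comparator members who "have already completed responding to the four administrations of the pre-intervention questionnaire"; 6.6.2.1 implies a 12-month schedule. For Stage 2, 6.3.8 gives baseline plus two-monthly for a year, while 6.9.2 counts up to six administrations.

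**The concern.** If the trial shows no difference, the first question will be whether control patients benefited because their clinicians had learned from the intervention arm. The score comparison is the only quantitative one of the two checks in 6.3.6. It is informative only if the Stage 1 group really was cared for without QPSS influence, if its dependence on the control group is handled, and if both groups are compared over the same follow-up.

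As written, none of the three is secured. By the protocol's own definition, contamination arises when clinicians who have used the QPSS change how they assess their other patients. That can begin in the transition phase, among patients who are still supplying comparator data. It would raise the comparator towards a contaminated control group and so make contamination look smaller than it is.

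**Working it through.** **1. The plan's own sample size.** Section 6.9.2.1 gives 432 and 158, then proposes 540 as three groups of 180. A one-way ANOVA with three independent groups and two-sided alpha 0.05 reproduces both figures: N = 432 at Cohen f = 0.15 (power 0.801) and N = 158 at f = 0.25 (power 0.802). The values of f and the 80% power are assumptions, because the protocol states neither. Then 432 / (1 − 0.20) = 540, with 20% attrition inferred. On this reading the comparator is 180 separate people, which 6.4.2.5 and 6.5.2.3 do not ensure.

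**2. Calendar overlap.** Transition occupies the last six of 12 months, so 6/12 = 50% of the window described as preceding use. Take the transition to start after month 6, visits to be on time, and the first of four administrations to be baseline:

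| Enrolled at Stage 1 month | Four administrations fall at months | After month 6 |
|---|---|---|
| 0 | 0, 2, 4, 6 | 0 of 4 |
| 2 | 2, 4, 6, 8 | 1 of 4 |
| 4 | 4, 6, 8, 10 | 2 of 4 |
| 6 | 6, 8, 10, 12 | 3 of 4 |

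Anyone enrolled after month 6 has every questionnaire inside the transition period. Under the 12-month schedule, even a month-0 enrolee has months 8, 10 and 12 inside it (3 of 7).

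**3. Amount of direct use.** Over seven sites: 2 × 7 = 14 to 4 × 7 = 28 clinicians, and 14 × 1 = 14 to 28 × 2 = 56 patients. Section 6.4.2.4 can be read as 1 to 2 patients per site, that is 7 to 14. This counts users. The spillover to other patients is not known.

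**4. People in both groups.** With n per group, a shared fraction s and within-person correlation r, the variance of the difference in means is (2σ²/n)(1 − s·r). An unpaired analysis uses 2σ²/n, so true SE / assumed SE = √(1 − s·r). The protocol gives neither s nor r; the ranges below are assumptions.

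- s = 0.10, r = 0.3: √0.97 = 0.985; the actual type I error of a nominal 5% test is about 4.7%.
- s = 0.50, r = 0.7: √0.65 = 0.806; the actual type I error is about 1.5%.

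Ignoring the overlap makes the test too cautious, again in the direction of missing contamination. Re-enrolled people are also survivors whose illness has had longer to progress and who have answered the questionnaires before. A variance correction does not remove that.

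**5. Schedules side by side.**

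- Comparator: four administrations at two-month spacing span 3 × 2 = 6 months (6.5.2.2), against 12 months (6.6.2.1).
- Stage 2: months 0, 2, 4, 6, 8, 10, 12 are seven occasions (6.3.8), against up to six (6.9.2).

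**6. What the contrast estimates.** The control-minus-comparator difference is contamination plus health-system change plus any difference in who was recruited. One before/after difference cannot give its parts separately.

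**The case against.** The case on the other side has substance.

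- **Early use is small and partly fenced off.** A few clinicians per site are involved. Transition patients are chosen from people not then giving comparator data, and their own data are excluded. This limits the size of the problem, and six overlapping months do not mean six months of full exposure. It does not protect other patients of those clinicians. Choosing transition patients who are not currently supplying comparator data also presupposes that the two activities run together.
- **The aim is modest.** The protocol speaks of exploring contamination and adds a qualitative check that bears on its cause. A reader might infer that contamination could not be shown at all. The documents do not support that: exposure dilutes a difference without making it undetectable, and shared time points could still be compared.
- **The two schedule readings do not combine into a worst case.** With four administrations, the earliest enrolees finish before transition. With 12 months, overlap is larger but follow-up length matches Stage 2. The point is the unresolved contradiction; a shorter comparator schedule is not established.
- **Area under the curve.** A reader might infer that unequal schedules create a large artificial gap in that summary. Section 6.9.2 applies it, with analysis of covariance, to intervention versus control. The analysis there that names three groups is growth modelling, which tolerates unequal numbers of occasions, and 6.3.6 says only that scores are compared.
- **Power.** A reader might count low power for a small leak as part of this defect. It would be just as low with a clean comparator of the same size.
- **An analysis plan may exist.** Model details can be left to it. The enrolment window, who may be in each group and the number of questionnaires are protocol statements, and they conflict here.

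**Conclusion.** The point holds in a limited form: the comparison cannot reliably isolate or rule out contamination. The contradiction over the window, the permitted membership of both groups and the conflicting schedules are plain from the text. That one contrast cannot separate contamination from system change follows from its design.

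The size of the effect is uncertain. Half the stated window overlaps QPSS use, but by only 14 to 28 clinicians over seven sites. Ignoring shared people would overstate the standard error, with a true-to-assumed ratio between 0.81 and 0.99 under the assumed ranges. Both effects lean towards false reassurance. Health-system change could act in either direction.

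The randomised comparison of intervention with control is not biased by any of this. What suffers is the interpretation of a small or null difference.

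**What to change.** 1. Reconcile 6.1.1, 6.1.2, 6.2, 6.2.2, 6.2.3, 6.5.2.2 and 6.6.2.1 on when the pre-intervention group is enrolled and assessed and how many questionnaires it receives. Reconcile 6.3.8 with 6.9.2 on the number of Stage 2 occasions.
2. In 6.3.6 and 6.9.2, limit the contamination comparison to pre-intervention questionnaires completed before the site's transition start date, and record that date for each site.
3. Compare the two groups over the follow-up months they share.
4. Account for people in both groups, either with a person random effect that keeps one identifier across stages or by excluding them from one side. Report how many there are.
5. State that the contrast is descriptive and cannot by itself separate contamination from health-system change, and that it is to be read with the clinician interviews.

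No new participants or data are needed. The cost is that some Stage 1 questionnaires, and possibly some people, drop out of this one exploratory comparison, which lowers its precision.
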